#### Eligibility

Each newly referred patient is asked to answer the optional adjustment disorder section of the Mini International Neuropsychiatric Interview (MINI) [46], French version [47], to confirm he or she meets to the ADA criteria according the DSM-5. The MINI is administered during a face-to-face interview by clinical investigators who are trained in psychiatry. See Textbox 1 for selection criteria for study subjects.

#### Randomization

Immediately after inclusion and assessment, patients are randomly allocated in a 1:1:1 ratio into 3 groups using a Web-based central randomization: patients using a digital stress management module (group 1), patients following the stress management module guided by a therapist in attendance (group 2), and patients on a waiting list and benefiting from usual care through their attending physician (group 3).

The randomization sequence is provided by an independent statistician (who does not take part in assessing the patients at any point in the study) using computer-generated random numbers with block sizes of 6 and center stratification consistent with the Consolidated Standards of Reporting Trials (CONSORT) [48]. The randomization sequence is implemented in the electronic case report form (eCRF) system to ensure a centralized, real-time randomization procedure.

A document describing the randomization procedure is kept confidential in the Clinical Investigation Centre of Lille University Hospital.

#### Assessments

Assessments are conducted for the 3 groups at baseline, 2 months, and 6 months. At baseline, participants complete the self-administered questionnaires for anxiety and depressive symptoms, and care contacts and medications are recorded. At 2 and 6 months, an evaluation of overall satisfaction as well as adverse events is additionally carried out. Self-assessments are collected in the face-to-face sessions with the investigator.

It is the same psychiatrist investigator for each site who generated the random allocation sequence, enrolled the participants, assigned the participants to the interventions, and assessed the participants, so he is not blinded to the intervention group.

The flowchart in Figure 1 summarizes the experimental design.

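### The protocol names two different originators of the allocation sequence, an independent statistician and the unblinded enrolling psychiatrist, so it does not establish allocation concealment

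*Protocol article*

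**What the plan says.** The Randomization section states: "The randomization sequence is provided by an independent statistician (who does not take part in assessing the patients at any point in the study". The list is made "using computer-generated random numbers with block sizes of 6 and center stratification". Delivery is central: "patients are randomly allocated in a 1:1:1 ratio into 3 groups using a Web-based central randomization", and "The randomization sequence is implemented in the electronic case report form (eCRF) system to ensure a centralized, real-time randomization procedure". The section adds that the document describing the procedure is held confidentially at the Clinical Investigation Centre in Lille, and that allocation follows inclusion and the baseline assessment.

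The next section, Assessments, states: "It is the same psychiatrist investigator for each site who generated the random allocation sequence, enrolled the participants, assigned the participants to the interventions". The sentence continues "and assessed the participants, so he is not blinded to the intervention group".

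Type of Study confirms that the trial is unblinded. Recruitment lists three centers. The Discussion gives 50 of 120 participants enrolled at the time of writing.

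**The concern.** Concealment depends on the person deciding whether and when to enroll a patient not knowing the next allocation. The article gives two incompatible accounts of who held that knowledge, and in one of them the enroller made the list.

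The consequence would be selection bias. Patients come by referral and eligibility rests on a clinician-administered interview, so timing and inclusion leave some room for judgment. An enroller who can foresee a wait-list assignment can defer or decline a patient, or favor one for an active arm. The primary analysis of covariance adjusts for baseline STAI and center. That deals with imbalance in those two variables but not with unmeasured differences in motivation, expectancy or prognosis.

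This is not detail left to the full protocol or the SAP. The article makes two positive statements that conflict.

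**Working it through.** **1. The two accounts side by side**

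| Question | Randomization section | Assessments section |
|---|---|---|
| Who made the sequence? | Independent statistician | Psychiatrist investigator at each site |
| Does that person assess patients? | No, at no point | Yes |
| Does that person enroll and assign? | Not stated; allocation is central, through the eCRF | Yes |
| Concealed from the enroller? | Yes, if the system works as described | No |

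The second row alone rules out that both describe the same person. A central system does not reconcile them either: if the enroller wrote the list loaded into it, the system hides nothing from that enroller.

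**2. How much a fixed block would reveal, given the list itself is hidden**

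Inputs from the Randomization section: 3 arms, 1:1:1, "block sizes of 6 and center stratification". Each block therefore holds 2 patients per arm, and there are 6!/(2!·2!·2!) = 90 equally likely blocks.

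Assumptions that the article does not state: the investigator knows the block size, knows where each block starts, and sees every earlier allocation in the center.

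*Allocation fully known.* The 6th is always known. The 5th is known when the last two places belong to the same arm: 3 × (1/15) = 1/5. Positions 1 to 4 are never fully known. The average over the block is (0 + 0 + 0 + 0 + 1/5 + 1)/6 = 0.20.

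*Wait-list status known*, meaning it is certain that the next patient will, or will not, go to the wait list. The two wait-list places can fall in C(6,2) = 15 equally likely pairs of positions.
- Position 3: both already used, 1/15.
- Position 4: both among the first three, 3/15.
- Position 5: both among the first four, 6/15, or both still to come, 1/15; together 7/15.
- Position 6: 15/15.
- Average: (1 + 3 + 7 + 15)/15 ÷ 6 = 26/90 = 0.289.

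By full enumeration, at least one arm can be ruled out for 46.7% of allocations, and the best guess is right 56.1% of the time against 33.3% by chance. These two figures are weaker evidence: ruling out one arm is not knowing the allocation. The 28.9% bears most directly on the primary comparisons, each of which is against the wait list.

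**3. Recruitment count**

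50/120 = 41.7%, which agrees with the printed 42%. At the time of writing 120 − 50 = 70 patients were still to be randomized. The number remaining at publication is not given, so the percentages are not converted into patients.

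The sample size of 32 per group, raised to 40 for missing data, is unaffected.

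**The case against.** The strongest reply is that the Randomization section describes a sound procedure in full: independent generation, central real-time allocation, a confidential procedure document, and baseline assessment before allocation. The conflicting sentence sits under Assessments and serves to explain why the assessor is unblinded. Its verb may loosely describe triggering an allocation in the eCRF. This is plausible, and it is why the text does not support the reading that concealment failed. The conflict still stands, because the sentence names generation, enrollment and assignment as separate acts by one person.

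Three further inferences are tempting and not supported.

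- That investigators could in fact predict allocations. The article does not say that sites were told the block size before publication, and a single block size with central allocation and center stratification is a common design. The 20% and 28.9% are conditional.
- That 70 patients were exposed to a published block size. That is the count at writing; the inclusion period was 24 months from January 2016 and the number left at publication is unknown.
- That patients answered in front of the unblinded investigator. The article says "Self-assessments are collected in the face-to-face sessions with the investigator", but the same section describes the questionnaires as self-administered. Collection is not completion under observation. Response bias is a separate and weaker issue, and the lack of blinding is disclosed.

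**Conclusion.** The point holds as an internal contradiction about who generated the allocation sequence. It must be resolved, because one account gives concealment and the other gives none from the enroller. The supported conclusion is that the article does not establish concealment. A reader might go further and infer that it was broken; no statement in the article shows that.

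The block-size point is secondary. Under the knowledge assumptions listed with the calculation, and taking the article to mean one enrolling investigator per site, 20% of allocations would be certain and wait-list status would be known for 28.9%. If sites did not know the block size, these figures do not apply.

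**What to change.** 1. **Check, then correct.** Establish from the randomization records who generated the list at each center, and amend whichever section is wrong. The answer should not be presumed. State that site staff neither generated the list nor can access it, if the records bear this out. Cost: a records check and a text correction.

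2. **If a site did generate its own sequence,** disclose it and add a sensitivity analysis of the primary outcome without that site's patients. This costs precision. With equal recruitment (an assumption), dropping one of three centers leaves 120 × 2/3 = 80 patients, about 27 per arm before missing data, against the 32 per group the plan requires. If the sentence is literally true of every site, no patients would be left for such an analysis and disclosure is all that remains.

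3. **If patients remain to be randomized,** load a new center-stratified list with randomly varying block sizes, in multiples of three to keep 1:1:1, not disclosed to sites. Cost: one new list in the existing web system and a slight risk of arm imbalance within centers. The risk grows if few patients remain per center and larger blocks stay incomplete. If recruitment has closed, this step falls away.

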### Interventions

The content of the 2 programs is identical; one is delivered by computer and the other face-to-face. The details of the programs are presented in Table 1.

#### Computer-Based Stress Management Program

The program includes 5 weekly sessions lasting 1 hour that patients follow from a program accessible on a computer in our unit.

Participants have minimal contact with a clinician to encourage adherence and engagement with the program. This minimal contact of 5 minutes is performed before and after every session by a trained nurse, who investigates the adverse events and drug dose changes since the last session, answers any questions, discusses the progress of the session, and possibly guides participants in the navigation of the computer program.

To avoid connection problems, a flash memory drive is supplied to the participant at the first session that contains videos, audio files, self-help books, a portfolio in the form of an eGuide, and a log book with the program of exercises to be completed between 2 successive sessions of the program. The patient is encouraged to practice 1 or several daily exercises for 20 minutes each, 5 or 6 days per week (Multimedia Appendix 3).

Selection criteria.Inclusion criteria:Ambulatory patient (as inpatients are frequently a mixed anxiety depressive type of adjustment disorder)Male or female aged 18 to 60 years (we use a cutoff age of 60 years for inclusion to limit chronic somatic comorbidities)Diagnosis of adjustment disorder with anxiety (ADA) according to the *Diagnostic and Statistical Manual of Mental Disorders, Fifth Edition* criteriaCurrently not supported by structured psychotherapeutic treatment for ADA or any other problemTaking no new psychotropic drug therapy or stabilized for at least 3 months (in the latter case, the patient will be informed of the need to keep the same dosages for the duration of the study)Minimum score on the Hospital Anxiety and Depression scale (HADS) anxiety subscale greater than or equal to 10 and a maximum score on the HADS depression subscale of less than 10Access to a computerExclusion criteria:Inability to read or use a computer with support (the platform is easy-to-use and a nurse is available to guide the patient in the navigation of the computer program)Pregnancy (as recommended by the French ethics committee; urine pregnancy test performed on female patients)Not capable of consenting, not having legal protection, or being deprived of libertyDiagnosis of another psychiatric disorder (according to the Mini International Neuropsychiatric Interview)

**Figure 1 figure1:**
[figure not shown]
Flowchart of the study.

**Table 1 table1:** Seren@ctif content.

Module theme	Aims of the module	Content of the module
Introduction and education regarding stress and anxiety	Provide psychoeducation about stress and anxiety and their treatment; identify anxiety symptoms and discuss treatment goals and expectations.	Psychoeducation about stress and anxiety (the model of the cognitive emotional stress spiral from a concrete example of stressful situations in everyday life); query about anxiety symptoms, treatment goal and expectations. Daily exercise: anxiety monitoring.
Body relaxation	Introduce different relaxation techniques and their respective targets and learn to practice them.	Different relaxation techniques: deep breathing, progressive muscle relaxation, and imagery and their relevance to stressful situations. Daily exercise: podcasts.
Cognitive therapy	Introduce the concept of changing thoughts; explain common thinking errors, alternative thoughts, and coping statements; practice.	Cognitive work on automatic thoughts based on concrete situations in everyday life; rationalization of the content of thoughts through cognitive restructuring and identification of repetitive negative ruminations. Daily exercise: identify dysfunctional automatic thoughts and search for other less stressful thoughts.
Mindfulness	Understand the interest in accepting rather than repressing emotions to focus attention on the present moment; focus on sensations to relieve negative thoughts and sensations.	Direct attention to breathing and bodily sensations to overcome stressful thoughts and accept the world and its surrounding thoughts. Daily exercise: podcasts.
Exposure and developing positive attitudes	Introduce the concept of changing behavior and practice it.	Principles of problem-solving, exposition, time management, planning pleasant activities, developing empathy, better assertiveness, exercise of full consciousness by concentration on the present moment.

#### Stress Management by Face-to-Face Interviews

The program includes 5 weekly sessions lasting 45 minutes or 1 hour with trained clinical psychologists (graduate of a master’s program in cognitive and emotional therapy with a minimum of 1 year of practice in CBT and cognitive behavioral stress management). Information, exercises, and homework assignments are delivered by the therapist without self-help support. At the beginning of each session, the therapist asks the participant about adverse events and changes in drug doses since the last session.

#### Wait List Control

Control group patients received usual care consisting of contact with their general practitioner and nonspecific psychoeducation about stress and anxiety. Medication is prescribed as a stable dose during the period prior to assessment at 2 months.

### Outcome Measures

We used the French version of self–report measures for which reliability and validity have been demonstrated.

#### Anxiety

Spielberger State Trait Anxiety Inventory (STAI)–Form Y Trait version [49]. The French adaptation by Bruchon-Schweitzer and Paulhan [50] is a 20-item questionnaire with 4 levels of ratings from 1=not at all to 4=much (total score of 20 to 80) that captures how the subjects feel generally (9 reversed items).Hospital Anxiety and Depression Scale (HADS). This questionnaire queries anxiety and depressive disorders using 14 items rated on a 0 to 3 scale with 7 questions relate to anxiety (total A). A score between 8 and 10 on each of the subscales is considered a risk (possible or probable) of anxiety or depressive disorders [51]. The French version is used [52].Penn State Worry Questionnaire (PSWQ). This is a self-assessment questionnaire consisting of 16 items measuring the general tendency to worry with answers based on a 5-point Likert scale ranging from 1=not at all characteristic to 5=extremely characteristic (scores range from 16 to 80) [53]. A French version of the PSWQ is used [54].

#### Stress

Perceived Stress Scale (PSS) comes from the stress transactional model and contains 14 items. The total score ranges from 0 to 56, and higher scores represent higher stress levels. Two dimensions emerge from this scale: perceived threat and perceived personal effectiveness [55]. The French version is used [56].Visual analog scale of stress (VAS-stress) is often used to measure the intensity of various symptoms, especially pain. It was used for the first time in 1996 for a subjective assessment of stress. The simplest VAS scale is a horizontal segment whose ends are defined as the limits of the parameter to be measured, oriented from the best to the worst. A study found external validity for the French version of VAS-stress by comparing its scores with the PSS, and it has a good sensitivity/specificity ratio [57].

#### Depression

Abbreviated Beck Depression Inventory (BDI) is a self-assessment questionnaire measuring the severity of depression with 13 items rated from 0 to 3 [58,59].Hospital Anxiety and Depression Scale (HADS) assesses anxiety and depressive disorders using 14 items rated 0 to 3 with 7 questions relative to depressive symptoms (total D). A score between 8 and 10 on each of the subscales is considered a risk (possible or probable) of anxiety or depressive disorders [52].

#### Interview for Diagnosis of Psychiatric Disorders

The Mini International Neuropsychiatric Interview Version 5.0.0 (MINI) is a fully structured diagnostic interview that assesses a major axis for the diagnosis of disorders [46]. Each newly referred patient was asked to answer the optional adjustment disorder section of the MINI from the French version [47]. The MINI was administered by research assistants who were trained to established reliability criteria. Any participant who met diagnostic criteria for a DSM-5 Axis I diagnosis was excluded from the study. There was no major change between DSM-IV and DSM-5 for anxiety and depressive disorders.

#### Satisfaction

The visual analog scale of satisfaction (VAS-satisfaction) measures the overall satisfaction with the program.

#### Main Criterion

The change in the STAI scale between baseline and the 2-month visit was the main criterion. We chose this criterion because it is a self-report measure, and self-report is commonly used in CBT and seems particularly indicated for Internet-based interventions [60]. In addition, the trait of anxiety is the core of a diagnosis of ADA, and the STAI-T measures the trait of anxiety, which is distinguished from a state of anxiety. The HADS scale and the Hamilton Anxiety Rating scale do not make this distinction.

#### Secondary Criteria

Change in the STAI scale between baseline and the 6-month visitChanges in other validated self-report measures of anxiety and worry at 2 and 6 months (HADS anxiety subscale, PSWQ)Changes in validated self-report measures of stress at 2 and 6 months (VAS-stress, PSS)Changes in validated self-report measures of depression at 2 and 6 months (BDI, HADS depression subscale)Consumption of tobacco (number of cigarettes smoked per day), alcohol (number of drinks of alcohol per week—in France, the standard drink contains 10 grams of alcohol) and drug use (days per week for each product) at 2 and 6 monthsVAS-satisfaction at 2 and 6 months for the 2 therapeutic groups and at 6 months for the WLC group

#### Sample Size

In a study on the clinical and psychometric characteristics of ADA, the mean (standard deviation) of the STAI baseline score was 52.1 (SD 14.6) [4]. Two clinical studies with patients with generalized anxiety disorder, 1 comparing CBT with relaxation [61] and the other comparing CBT with brief psychodynamic psychotherapy [62], showed changes in the STAI-T scores of 7 and 16, respectively. In view of these results, we hypothesize that an average difference between each experimental arm and the control arm of 11.5 (the mean of 7 and 16). To demonstrate this difference in variation with a standard deviation of the STAI score change of 14.6 (assuming a conservative correlation coefficient of 0.5 between the baseline and 2-month STAI measures), a 2.5% type I error (using a Bonferroni correction for the 2 prespecified comparisons), and a power of 80%, it is necessary to include 32 patients per group. Although analysis of the primary outcome will be adjusted for baseline values, the sample size calculation does not take into account this adjustment to maximize the power. Finally, considering 20% ​​missing data, 120 patients (40 per group) are planned in this clinical trial.

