### Adjustment Disorder With Anxiety

#### Definition

Adjustment disorder with anxiety (ADA) is the most frequent and best characterized stress-related psychiatric disorder [2]. According to the *Diagnostic and Statistical Manual of Mental Disorders, Fifth Edition* (DSM-5), a diagnosis of ADA is appropriate with the finding of anxiety occurring within 3 months of a psychosocial stressor or life event (eg, divorce, job loss, serious physical illness) [3] with symptoms generally abating by 6 months after the event. Considered a common disorder ranging from mild to moderate intensity, ADA is a true diagnostic entity. A general medical study showed that the level of anxiety is comparable to that of other anxiety disorders such as generalized anxiety disorder [4].

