#### Current Recommendations for Adjustment Disorder With Anxiety

Patients are generally not treated with a tailored approach but with medication, mainly benzodiazepine monotherapy. Benzodiazepine misuse is a public health problem. Although stress management is considered the most appropriate psychological treatment for ADA, the evidence base for this approach is limited [5] **.** However, several studies compared cognitive behavioral therapy (CBT) with other treatments for generalized anxiety disorders and found greater improvements in stress and anxiety symptoms from CBT. In a study comparing CBT with relaxation, a posttreatment progression for State-Trait Anxiety Inventory scale (STAI-T trait subscale) scores from 53.04 to 46 and for Penn State Worry Questionnaire (PSWQ) scores from 61 to 51.13 were shown for the group that received CBT [6]. A study comparing psychodynamic psychotherapy with CBT found a greater improvement in the symptoms of stress and anxiety for the CBT intervention (a posttreatment progression of STAI-T trait subscale scores from 58.83 to 43.41 and of PSWQ scores from 63.48 to 49.86 in this group) [7]. In addition, eMental health options are considered uniquely suited for offering early intervention after patients experience stressful life events that can potentially trigger adjustment disorders [8].

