### Digital Stress Management

In recent years, the development of new technologies has enriched self-help programs by integrating new tools (CD-ROM, flash memory drive, or directly accessible on the Internet), allowing better interactivity and use other than contact with the therapist for patients [20].

These computer-assisted programs are intended to limit the amount of contact time with a mental health professional [21-23]. They have been evaluated in many countries in general, student, and corporate populations [24-36]. Unfortunately, computer-assisted programs have not been evaluated in France.

Recently, a meta-analysis evaluating the effect sizes of 26 computer- and Internet-based interventions was conducted on psychological stress and found significant results in terms of reduction of symptoms of stress (Cohen *d*=0.43, 95% CI 0.31-0.54), depression (Cohen *d*=0.34, 95% CI 0.21-0.48), and anxiety (Cohen *d*=0.32, 95% CI 0.17-0.47) compared to other types of interventions. These results provide evidence that Web- and computer-based stress management interventions can be effective and have the potential to reduce stress-related mental health problems on a large scale [37].

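### The planned 11.5-point difference from the wait list is an average of pre-to-post changes within CBT groups, so the stated 80% power silently assumes no wait-list improvement

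*Protocol article*

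**What the plan says.** In the protocol article, Sample Size, two clinical trials in generalized anxiety disorder, one of CBT against relaxation and one of CBT against brief psychodynamic psychotherapy, "showed changes in the STAI-T scores of 7 and 16, respectively". The planning difference follows directly: "we hypothesize that an average difference between each experimental arm and the control arm of 11.5 (the mean of 7 and 16"). The spread is "a standard deviation of the STAI score change of 14.6 (assuming a conservative correlation coefficient of 0.5 between the baseline and 2-month STAI measures"). With a 2.5% type I error per comparison and 80% power, this gives 32 per group, raised to 40 per group (120 in all) for 20% missing data. The section discloses that the gain from baseline adjustment was left out of the calculation.

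The Introduction (Current Recommendations for Adjustment Disorder With Anxiety) describes two trials with the same pair of comparisons. For CBT against relaxation, STAI-T "scores from 53.04 to 46" "were shown for the group that received CBT". For CBT against psychodynamic therapy it reports "a posttreatment progression of STAI-T trait subscale scores from 58.83 to 43.41", again in the CBT group.

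The control arm (Wait List Control) has general practitioner contact and nonspecific psychoeducation. The Definition section describes the disorder as one "with symptoms generally abating by 6 months after the event". The primary test (Main Objective) is an ANCOVA adjusted for baseline STAI and center, at 2.5% for each experimental arm against control.

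**The concern.** A change from before to after treatment in one arm contains the treatment effect and everything else that moves the score: natural course, usual care, and repeated measurement. A between-arm difference contains only what is left after the control arm's change is removed. The two are equal only if the control arm does not change. Both source trials had active comparators and the article quotes only their CBT groups, so neither figure, as presented, is a difference from a wait list. No control change is stated, subtracted or argued to be zero.

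The article's own description of the disorder and of the control condition makes some wait-list improvement likely. If it occurs, the net difference is smaller than 11.5 and the trial has less power than stated for both primary comparisons. A non-significant result would then be read against an 80% that the design may not deliver.

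**Working it through.** **Inputs.** Difference 11.5; SD of change 14.6; baseline SD 14.6; correlation r = 0.5; alpha 2.5% per comparison; power 80%; 32 per group; 20% missing (all from Sample Size). ANCOVA on baseline and center (Main Objective). Wait-list improvement w: not in the article, so assumed and shown as a range.

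**1. Origin of 11.5.** (7 + 16)/2 = 11.5. The CBT-group scores in the Introduction give 53.04 − 46 = 7.04 and 58.83 − 43.41 = 15.42. Comparators and sizes correspond to the 7 and 16, so these are within-arm changes. (The mean of 7.04 and 15.42 is 11.23, which is a small side discrepancy.)

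**2. The plan's own figure.** SD of change = 14.6 × √(2 × (1 − 0.5)) = 14.6, as stated. For a two-sample t test with n = 32 per arm, the standard error is 14.6 × √(2/32) = 3.65 and the noncentrality is 11.5/3.65 = 3.15. With 62 degrees of freedom and two-sided alpha 0.025 (critical value 2.297), power is 80.1%; n = 31 gives 78.7%. So 32 reproduces, and 32/0.8 = 40 per group, × 3 = 120. The smallest difference with 80% power is 11.49, so the unadjusted calculation has practically no slack.

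**3. The planned ANCOVA.** Residual SD = 14.6 × √(1 − 0.5²) = 12.64. This ignores the small cost of the center term. At 11.5 points, power is 91%. The difference with 80% power is 9.95, so ANCOVA tolerates 11.5 − 9.95 = 1.55 points of wait-list improvement.

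**4. Power when the wait list improves by w.** Net difference = 11.5 − w, 32 evaluable per arm, two-sided 2.5%:

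| w (assumed) | Net difference | Unadjusted | ANCOVA, r = 0.5 |
|---|---|---|---|
| 0 | 11.5 | 80% | 91% |
| 1 | 10.5 | 72% | 84% |
| 2 | 9.5 | 62% | 76% |
| 3 | 8.5 | 52% | 65% |
| 4 | 7.5 | 41% | 53% |
| 5 | 6.5 | 31% | 41% |

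**5. Sensitivity to r.** At w = 3, ANCOVA power is 65% for r = 0.5, 73% for r = 0.6 and 83% for r = 0.7. The last two r values are assumptions; the article calls 0.5 conservative.

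**6. Optional figure for the digital arm.** The planning effect is 11.5/14.6 = 0.79 SD. The Digital Stress Management section cites "anxiety (Cohen *d*=0.32, 95% CI 0.17-0.47) compared to other types of interventions". If one assumes that this d applies here and converts at SD 14.6, then 0.32 × 14.6 = 4.67 points (power 16% unadjusted, 21% ANCOVA) and 0.47 × 14.6 = 6.86 points (35%, 45%).

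**The case against.** The strongest reply is that the trial will not run the unadjusted test. The planned ANCOVA has 91% power at zero wait-list change, and the article says openly that this gain was left out. That stands. A reader might infer that 80% power is lost as soon as wait-list patients improve at all. This is true only of the unadjusted calculation. With ANCOVA, about 1.5 points of improvement are absorbed at r = 0.5, and more if r is higher.

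A reader might also infer that the article contradicts the zero-change assumption. It does not go that far. The natural-course statement is tied to 6 months after the stressor and gives no STAI-T change at 2 months after enrolment. The article also chose the trait scale because it is distinct from state anxiety. These points leave zero change implausible but the true change unquantified.

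Nor do the documents show that the digital comparison is underpowered. The cited meta-analysis compared with other types of interventions, not a wait list. The conversion to STAI-T points is an assumption, and 0.47 is the upper confidence limit of a pooled mean, not a ceiling for this program. The Cognitive Behavioral Therapy section cites d = 0.53 for workplace stress-management programs and d = 1 for structured CBT-based ones, and the planned 0.79 lies between them. At d = 1, unadjusted power is 95%.

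Finally, the two sections number their references differently, and 15.42 does not round to 16. The link between them therefore rests on matching comparators and sizes. The side figure of 11.23 (78% unadjusted, 89% ANCOVA) should carry no weight. If the program arms improve by more than 11.5, some wait-list improvement would be offset, but the article does not argue this.

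**Conclusion.** The point holds as a flaw in an input assumption; the arithmetic is correct. A within-arm quantity has been used as a between-arm one, and the stated 80% power depends on an undeclared absence of wait-list change. If the program arms improve by 11.5 points and 32 per arm are evaluable, a 3-point wait-list improvement leaves 52% power unadjusted and 65% with ANCOVA, and a 5-point improvement leaves 31% and 41%. These losses rest on assumed values of w and on r = 0.5. For improvements up to about 1.5 points, the planned ANCOVA still delivers 80%. The statement should be corrected, but the design need not change: the article already commits to reporting mean differences and effect sizes with confidence intervals, which partly guards against misreading a null result.

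**What to change.** Keep 120 patients and revise the Sample Size text:

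- State that 11.5 is derived from changes within CBT groups and is a net difference only if the wait list does not change. Alternatively, justify 11.5 as a net difference on other grounds.
- Restate what the design detects with 32 evaluable per arm at two-sided 2.5%: 80% power for a net between-arm difference of 11.5 points unadjusted, or about 10 points (9.95) with the planned ANCOVA at r = 0.5.
- Give power over a range of wait-list improvements, for example 0 to 5 points as in the table, labelled as assumptions.
- Optionally, add digital-arm power at d = 0.32 to 0.47 (16–35% unadjusted, 21–45% ANCOVA). Label it as an assumption, with the caveat on the comparator and a mention of the larger effects that the article also cites.

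The cost is rewording and a less favourable power statement. Patient numbers, alpha and the analysis stay as they are. With 50 of 120 patients recruited when the article was written, the change could be made before results were known.
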